### Interim analyses {21b}

No interim analyses are planned.

### Methods for additional analyses (e.g., subgroup analyses) {20b}

There will be no additional analyses.

### Methods in analysis to handle protocol non-adherence and any statistical methods to handle missing data {20c}

Non-adherence to the protocol will be assessed from the intervention log entered by each investigator/clinical coordinator who administers the intervention at each study performance site. If more than 5% of the experimental data values are missing, values will be encoded as − 1 or − 9999, replaced with the mean/median value, encoded as another level of a categorical variable and predictive models that impute the missing data will be applied [95].

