### Trial design {8}

This is a mechanistic, sham-controlled, randomized, parallel design, multi-site (2 sites), clinical trial in which participants with chronic SCI are assigned in equal ratios to one of three study groups (or arms). Group 1: Active transspinal stimulation while standing followed by locomotor training; Group 2: Active transspinal stimulation while lying supine followed by locomotor training; and Group 3: Sham transspinal stimulation while standing followed by locomotor training. Study outcomes are assessed for superiority before (baseline) and after 40 sessions of primed locomotor training.

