#### Secondary outcomes

The secondary outcomes include the International Standards for Neurological Classification of SCI (ISNCSCI) sensory and motor scores, temperature sensation, proprioceptive sensation, ability to stand and walk, and autonomic function. Standing and balance ability is evaluated with the Berg Balance Scale [77, 78] and BEST tests [79]. Walking capacity is tested with the 2-min and 10-m walking tests [80]. A combination of validated questionnaires related to bladder, bowel, and sexual function are used to assess autonomic function [81–87].

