The soleus H-reflex amplitude during assisted stepping in 11 persons with motor incomplete SCI (AIS C-D) recorded from the right leg was compared before and after locomotor training [26]. Based on the amplitude of the soleus H-reflex at mid-stance before and after training (difference in means of pre versus post: 13.67, pooled standard deviation: 17.4), the effect size was 0.79. To predict sample size at a power of 0.80 at α = 0.05 using a one-way ANOVA across 3 groups, 21 total subjects are needed. We will enroll 45 subjects, so we will be adequately powered even if subjects drop out at a higher than expected 20% rate.

Limb coordination relies on the strength of reciprocal inhibition between antagonistic muscles. We used data from a study performed by our group that examined short-latency inhibition from ankle flexor afferents onto ankle extensor motoneurons at rest in 13 persons with AIS C-D SCI before and after locomotor training [28]. Based on the amplitude of the conditioned H-reflex at the conditioning-test interval of 2 ms before and after training (difference in mean of pre versus post: 15.04, pooled standard deviation: 17.21), the effect size was 0.874. To predict sample size at a power of 0.80 at α = 0.05 using a one-way ANOVA across 3 groups, 18 total subjects are needed. We will enroll 45 subjects, so we will be adequately powered even if subjects drop out at a higher than expected 20% rate. Please note that the established power was based on data from SCI subjects who received either transspinal stimulation or locomotor training separately and not combined.

*Aim 3*: Determine if priming locomotor training with high-frequency transspinal stimulation improves limb coordination and the ability to stand and walk. These are secondary measures, and the study is not powered based on these outcomes.

Collectively, an average of 6 to 8 subjects per group is needed to establish significant differences for primary outcomes before and after transspinal stimulation or locomotor training. By enrolling 15 participants per group, the study will be robustly over-powered to detect these differences despite a projected possible 20% dropout rate, sporadic missing data values, or lower-than-expected observed effect sizes.

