## Statistical methods

### Statistical methods for primary and secondary outcomes {20a}

For each dependent variable (primary and/or secondary outcome), descriptive statistics including frequencies and percentages for categorical variables and means and percentile distributions for continuous variables to examine the distribution of outcomes and describe the study population are performed.

We will group each dependent variable based on the time of testing (before and after the intervention) and the subject group (2 experimental, 1 sham). A two-way mixed analysis of variance (ANOVA) along with Bonferroni post hoc* t-*tests [93] at 2 3 levels (2: time, 3: groups) to test the main and interaction effects among subject groups and time will be performed separately for each outcome. Furthermore, repeated measures analysis of covariance (ANCOVA) will be performed for each outcome separately with gender, age, level of SCI, and clinically evaluated baseline walking function as separate covariates. Outcomes will not be analyzed based on SCI severity because the ISNCSCI scale does not correlate with improvements in walking ability [3], while age is considered one of the predictors of ambulation in SCI [94].

Mixed regression methods and analysis of slope and threshold of correlation will be used to establish the relationship between the ability to stand and walk, quality of life, and changes in primary outcomes (neurophysiological biomarkers). We will use an identity or log link based on the data distribution.

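### The missing-data rule fills missing values with a mean or median before the mixed ANOVA and gives no rule for choosing among the treatments it lists

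*Protocol article*

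**What the plan says.** Protocol article, section {20c}, sets a condition, "If more than 5% of the experimental data values are missing", and then lists what follows. First, "values will be encoded as − 1 or − 9999". The same sentence continues that they will be "replaced with the mean/median value, encoded as another level of a categorical variable and predictive models that impute the missing data will be applied". It does not say which treatment applies to which variable, or whether the mean or median is taken overall, by arm or by time point.

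The analysis that receives these values is in section {20a}: "A two-way mixed analysis of variance (ANOVA) along with Bonferroni post hoc" t-tests, with two times and three groups, run separately for each outcome. Section {20b} adds: "There will be no additional analyses". Participants are "assigned in equal ratios to one of three study groups", 15 per group, and the closing paragraph of Sample size {14} calls the trial over-powered "despite a projected possible 20% dropout rate, sporadic missing data values".

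**The concern.** A mean put in place of an unobserved value is then counted as an observation. If it is the arm's own mean, the within-arm spread is understated and the F test rejects too often. If it is the mean over all arms, each filled participant pulls the arms together and a true effect is diluted. The sentence permits either, so the direction of the error is open. Under {17b} data are unblinded when between-group tests are due, so a choice still open at that point could be made with allocation known.

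Two other elements do not fit the data. An extra category level has no meaning for the primary outcomes, which are continuous amplitudes and ratios. Numeric codes do harm if they are analysed as numbers. Predictive imputation could be acceptable by itself, but the sentence does not select it.

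**Working it through.** **Inputs from the protocol.** 15 per arm in three arms; 20% dropout as a possibility; alpha 0.05; for the H-reflex at 1.0 Hz, a difference of 25.28 and a pooled SD of 28.92. The protocol's effect size reproduces: 25.28 / 28.92 = 0.874, stated as 0.87.

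**Assumptions of mine.** Bivariate normal pre and post values with equal SD; pre-post correlation ρ of 0.3, 0.5 or 0.8; post values missing at random; the 0.87 SD effect in one arm and none in the other two. The protocol's 0.87 is a pre-post change in 6 people, so it only sets a scale here. The power figures are for comparing methods with each other, not for checking the sample size.

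**Does the trigger fire?** 20% of 15 is 3 per arm, so 9 of 45 post values are missing. Counting pre and post values, that is 9 / 90 = 10%, above 5%. At 10% dropout, 4.5 / 90 = 5%, which is not more than 5%.

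**Overall-mean fill.** A filled arm's post mean is (12 × observed arm mean + 3 × overall mean) / 15. The overall mean cancels between arms, so every between-arm difference is multiplied by 12 / 15 = 0.80. The effect becomes 0.87 × 0.80 = 0.70, a loss of 20% at any ρ.

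**Arm-mean fill.** The difference stays unbiased, but the spread does not. For the post values of one arm, the sum of squares is unchanged while it is divided by 14 instead of 11, so the variance falls to 11 / 14 = 0.79 of its observed value. The sample size is counted as 15 instead of 12. The naive standard error of that post mean is therefore √(0.786 × 12 / 15) = 0.79 of what the observed data support.

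**Simulation.** With two time points, the time-by-group F equals the one-way F on change scores, so that test was used.

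| ρ | Type I error, observed pairs | Type I error, arm-mean fill | Power, observed pairs | Power, overall-mean fill |
|---|---|---|---|---|
| 0.3 | 5% | about 9% | 0.40 | 0.35 |
| 0.5 | 5% | about 9% | 0.55 | 0.45 |
| 0.8 | 5% | about 8% | 0.93 | 0.73 |

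A repeat with 20,000 trials per row agreed to within 0.01. Overall-mean fill kept type I error near 5%. A separate run at ρ of 0.5 and 0.8, with missingness drawn at random at 20% per arm or at 7/20/33%, gave type I error of 7.6–9.5% for arm-mean fill and attenuation of 16–21% for overall-mean fill.

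The power loss grows with ρ for a simple reason. An observed change has variance 2(1 − ρ)σ², which is 1.4, 1.0 and 0.4 σ² at the three correlations. A filled change is roughly a constant minus the baseline value, with variance σ². At ρ = 0.8 each filled participant is noisier than an observed one as well as pulled toward the overall mean.

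**Numeric codes, if analysed as values.** Taking an assumed mean of 60, one −9999 among 15 gives (14 × 60 − 9999) / 15 = −611. With 20% missing in each arm, power is then about 4%. With −1 it is 32% at ρ = 0.5 and 46% at ρ = 0.8, so the two codes do not behave alike.

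**The case against.** Several points on the other side stand.

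A reader might infer that −9999 enters the ANOVA and wrecks it. The document does not say so. Read in sequence, the value is flagged with a code and the code is then replaced. The −611 figure shows what happens if that step is missed; it is not what the plan prescribes.

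A reader might also infer that the 5% trigger is bound to be met. It is met at 20% dropout, but the protocol calls that rate possible and, elsewhere in {14}, higher than expected. At about 10% dropout or less it might not be met.

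Since "Walking capacity is tested with the 2-min and 10-m walking tests", a reader might infer that people who cannot walk will be credited with average walking. Nothing says that inability is recorded as missing. The rule covers experimental data, which Data management {19} distinguishes from clinical data. For MEPs, the Primary outcomes section already limits the main outcomes to participants with obtainable soleus MEPs at baseline. What remains open is a response that is absent after therapy.

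It is also fair to say that the list may be meant as options by variable type, and that operational detail can sit in an analysis plan not shown here. That softens any charge of flat contradiction. It does not rescue mean or median replacement, which the protocol itself names as a treatment to be applied.

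**Conclusion.** The point holds for single mean or median replacement and for the missing selection rule. At 3 of 15 post values missing per arm, arm-mean fill takes type I error from 5% to about 8–9%. Overall-mean fill cuts the effect by 20% and costs 0.05 to 0.20 of power across ρ from 0.3 to 0.8. The 20% attenuation is arithmetic. The type I error and power figures rest on normality, random missingness, the assumed ρ and an effect in one arm only. The extra category level is inapplicable to the continuous primary outcomes. The documents do not support the claims that the numeric codes destroy the analysis, that the trigger is certain to be met, or that non-walkers will be given average scores.

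**What to change.** Rewrite the sentence in {20c} before unblinding:

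- State that −1 and −9999 are database flags and are never analysed as numbers.
- Delete the mean/median fill, the extra category level for outcomes, and the 5% trigger.
- Analyse all randomised participants with any measurement using one likelihood-based mixed model (arm, time, arm-by-time) under missing at random.
- Name multiple imputation by arm as the sensitivity analysis. Ideally include a shift away from missing at random, since imputation under that assumption does not test it.
- State, outcome by outcome, how an absent response or inability to perform a test is told apart from dropout. Avoid a blanket zero score: it leaves the 1.0/0.1 Hz ratio and the percent-of-control H-reflex undefined when the denominator is zero, and it could count an absent reflex as the hypothesised benefit.

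The cost is a paragraph of wording, a matching edit to {20a} because the mixed model replaces the ANOVA, and slightly more analysis work. With complete data the two agree.

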### Plans to give access to the full protocol, participant level-data and statistical code {31c}

Deidentified, individual-level data will be deposited to appropriate public repositories such as the Open Data Commons for Spinal Cord Injury (https://scicrunch.org/odc-sci). This will allow meta-analysis of disparate smaller studies; a need which is even more urgent in neurorehabilitation than in other fields that are more amenable to large drug studies.

## Oversight and monitoring

### Composition of the coordinating center and trial steering committee {5d}

The principal investigators (PIs) of this clinical trial are PI # 1, [name], PT, MBA, PhD, at the College of Staten Island, City University of New York, and PI # 2, [name], PhD, at Icahn School of Medicine at Mount Sinai and James J. Peters Veterans Affairs Medical Research Center (JJPVAMC). PI # 1 performs along with her research team at the Klab4Recovery all neurophysiological recordings before and after training for all study participants of the clinical trial to ensure consistent experimental procedures for all neurophysiological recordings. PI # 1 also leads the implementation of transspinal stimulation and locomotor training interventions, as well as the clinical assessments before and after training for study participants at Klab4Recovery. PI # 2 leads the implementation of transspinal stimulation and locomotor training interventions as well as the clinical assessments before and after training for study participants at JJPVAMC. Both PIs ensure that locomotor training and transspinal stimulation are implemented equivalently at both sites. The trial steering committee is composed of the PIs and dedicated research staff.

### Composition of the data monitoring committee, its role and reporting structure {21a}

The data and safety monitoring board (DSMB) committee includes 4 faculty from the City University of New York and are IRB-approved to serve as members of the DSMB. The DSMB members provide description of stopping rules and justification for the stopping rules, prospectively identified criteria for discontinuing the study, and determination of UEs, AEs, and SAEs. The DSMB committee is independent from the sponsor.

### Adverse event reporting and harms {22}

Recording of AEs, SAEs, serious unexpected adverse events (SUAEs), or unanticipated problems (UPs) occurs at all visits as reported by a participant or observed by study personnel and reported to the PIs. All events are recorded, while SAEs, SUAEs, and UPs are reported immediately to the IRB and DSMB. AEs are recorded and submitted to the study sponsor and to the reviewing IRB at the next annual review date. In case of occurrence or report of a SUAE, the PIs will complete an SUAE form and submit to the study sponsor and to the reviewing IRB as soon as possible, but within 5 working days after the PI first learns of the incident.

For incidents or events that meet the Office for Human Research Protections (OHRP) criteria for UPs, a UP report form will be completed and submitted to the IRB and to the NIH. The UP report will include the following information: protocol identifying information: protocol title and number, PIs name, and the IRB project number; a detailed description of the event, incident, experience, or outcome; an explanation of the basis for determining that the event, incident, experience, or outcome represents an UP and whether it is probably, possibly, or unlikely to be study-related; a description of any changes to the protocol or other corrective actions that have been taken or are proposed in response to the UP. To satisfy the requirement for prompt reporting, UPs will be reported using the following timeline: UPs that are SAEs will be reported to the IRB and to the NIH within two days of the investigator becoming aware of the event. Any other UP will be reported to the IRB and to the study sponsor within ten days of the investigator becoming aware of the problem. All UPs will be reported to appropriate institutional officials (as required by an institution’s written reporting procedures), the supporting agency head (or designee), and OHRP within 10 days of the IR’s receipt of the report of the problem from the investigator. Both PIs will be responsible for ensuring participants’ safety on a daily basis and for reporting all adverse events AE and UP to the IRB.

Based on our extensive clinical and research experience with SCI, transspinal stimulation, and locomotor training, we do not anticipate any SUAEs to occur. No safety issues have been reported following transcutaneous tibial nerve stimulation or following transcutaneous spinal cord (or transspinal) stimulation. In 38 out of 89 persons with SCI who received locomotor training with the Lokomat, adverse events included mild skin erythema at the sites of the cuffs, and muscle pain while open skin lesions (*n* = 2), joint pain (*n* = 2), or tendinopathy (*n* = 1) were also reported [96]. The events are predictable and are indicated as potential risks in the Informed Consent Form.

### Frequency and plans for auditing trial conduct {23}

Both PIs are responsible for ensuring participants’ safety daily and act in an advisory capacity to the NIH to monitor participant safety, evaluate the progress of the study, to review procedures for maintaining the confidentiality of data, the quality of data collection, management, and analyses. The PIs meet annually with the DSMB committee to review trial conduct.

Both PIs ensure that the experimental and training protocols are conducted as pre-determined and are responsible for the integrity and quality control of data. Quality control includes regular data verification and protocol compliance checks. All clinical data (including AEs, concomitant medications, and expected adverse reactions data) and clinical-laboratory data are entered into a 21 CFR Part 11-compliant data capture system. The data capture system includes internal quality checks, such as automatic range checks, to identify data that appear inconsistent, incomplete, or inaccurate. Monitoring of data is performed at both performance sites to ensure that the rights and well-being of trial participants are protected, that the reported trial data are accurate, complete, and verifiable, and that the conduct of the trial is in compliance with the approved protocol/amendment(s). Each site performs internal quality management of study conduct, data collection, documentation, and completion. An individualized quality management plan is developed to describe each site’s quality management. Internal audit is conducted by research staff. Meetings between the PI and research staff at each site hold at regular intervals and not less than once a week.

### Plans for communicating important protocol amendments to relevant parties (e.g., trial participants, ethical committees) {25}

Protocol amendments will be submitted for approval first to the Program Officer of the NICHD/NIH and then to the Institutional Review Board (IRB) before implementation. Following IRB approval, protocol amendments will also be submitted to ClinicalTrials.gov. Changes will be communicated to all investigators.

### Dissemination plans {31a}

#### Research findings and products

Research findings will be disseminated as publications in high-impact peer-reviewed academic journals and research summaries for clinical professional journals to provide the following milestones in clinical translational research. These milestones involve the identification of benefits (and drawbacks) by priming locomotor training with noninvasive transspinal stimulation in individuals with chronic SCI, and on the effectiveness of combined interventions on recovery of standing and walking ability in individuals with chronic SCI. Furthermore, a better understanding of the impact of transspinal stimulation based on body position will be provided. In addition to peer-reviewed publications, the results of the clinical trial will be submitted to ClinicalTrials.gov in compliance with the NIH policy requirements.

#### Dissemination goals

We aim to disseminate the findings of this study to scientists and patients and frontline clinical providers with the goal of improving quality of care, because noninvasive transspinal stimulation can be quickly transferred into different real-world clinical settings to reduce motor dysfunction after SCI and other upper motoneuron lesions in humans. Further, transspinal stimulation will be administered to patients in conjunction with locomotor training, supporting concomitant utilization of multiple interventions as occurs in real-life clinical rehabilitation settings.

#### Target audiences

There are four key audiences for this research: (1) patients and the public; (2) academia; (3) family physicians, physiatrists, physical therapists, and other frontline clinical staff; (4) external statutory organizations such as the Department of Health and the NIH. The PI has already developed and utilized a plan of targeting these end users by providing in-service research talks to local hospitals (4/year), hosting a research booth at the Abilities Expo in New Jersey attended by physicians, therapists, care givers, and patients. A barrier in trying to implement transspinal stimulation as treatment is that therapists and clinicians will require some basic form of training, which can be overcome by workshops.

#### Key message and communication avenues

The key message of this research study is the use of noninvasive transspinal stimulation to increase the effectiveness of traditional rehabilitation such as locomotor training in individuals with SCI and probably for other types of upper motoneuron lesions. This will change the standard of care promoting noninvasive approaches of rehabilitation relying on scientific evidence and not on anecdotal observations. We will communicate our key findings via the following avenues: *Broadcast media*: academic journals, book chapters, technical reports, regular newspapers, special interest newsletters, radio, or television interviews, websites, and social media such as Twitter, local and national SCI foundation newsletters, development of links with key SCI organizations. *Personal contact*: clinical specialty associations, informal professional networks, professional conferences, professional meetings (e.g., grand rounds), workshops, and other continuing medical education training.

